## Abstract

**Background and objective:**

Videolaryngoscopy have transformed airway management by improving intubation success rates compared to direct laryngoscopy. However, its widespread adoption has been hindered by the lack of standardized classification tools for documentation and communication. This manuscript outlines the rationale and study design of the VCISpain project, which aims to evaluate the interobserver reproducibility of the Video Classification of Intubation (VCI) scale in the context of airway management using videolaryngoscopy in Spain.

**Methods:**

This manuscript presents the planned methodology of the VCISpain study, a prospective, observational, multicenter, open-label study. The study will collect data on tracheal intubations performed in operating rooms, intensive care units, and emergency departments. In each case, two anesthesiologists will independently apply the VCI scale to assess blade type, Percentage of Glottic Opening (POGO), and ease of intubation.

**Ethics and registration:**

The study was approved by the University of Navarra Ethics Committee (2022.079 mod1) and registered on ClinicalTrials.gov (NCT06537531). It is endorsed by the Spanish Society of Anesthesiology, Resuscitation and Pain Therapy (SEDAR) and the European Airway Management Society (EAMS).

**Conclusions:**

VCISpain seeks to establish a standardized classification tool for documenting and communicating findings related to videolaryngoscopy in airway management. By presenting the study rationale and design, this protocol aims to promote transparency, ensure methodological rigor, and encourage broader discussion to refine the study prior to implementation.

## Introduction

Tracheal Intubation (TI) remains a cornerstone of airway management in both anesthesia and critical care, despite its routine use.^1^^,^^2^ Difficult intubation occurs in approximately 5%–8% of cases, while failed TI is reported in 0.05%–0.35% of cases.^3^ Recent data indicate a decline in these rates ‒ 1.6 and 0.06 per 1,000 cases, respectively ‒ primarily due to advances such as Videolaryngoscopy (VL).^4^ Nonetheless, airway management complications remain a significant cause of morbidity and mortality.^5^^,^^6^

Direct Laryngoscopy (DL) has traditionally been the gold standard for visualizing the glottis and guiding tracheal tube placement.^7^ The advent of VL in 2001 marked a significant milestone, reducing rates of difficult and failed airways.^8^ Consequently, several national and international societies ‒ including the American Society of Anesthesiologists (ASA), the Canadian Airway Focus Group (CAFG), and the Spanish Society of Anesthesiology and Resuscitation (SEDAR) ‒ now recommend VL as a first-line technique for TI due to its ability to reduce complications and improve clinical outcomes.^9^, ^10^, ^11^

Traditional classification tools ‒ such as the Cormack-Lehane scale, its modification by Yentis and Cook, and the Percentage of Glottic Opening (POGO) ‒ remain the most commonly used methods for assessing intubation difficulty.^7^^,^^12^, ^13^, ^14^ However, these tools were originally developed for direct laryngoscopy and may not fully capture the specific challenges associated with VL.^15^ For example, excellent glottic visualization (e.g., 100% POGO) during VL does not always guarantee procedural success^16^^,^^17^ due to difficulties in maneuvering and inserting the tube through the glottis.^18^, ^19^, ^20^ Although alternative scales have been proposed to overcome these limitations, none have gained widespread acceptance.^16^^,^^21^

The Video Classification of Intubation (VCI) scale was developed to address this gap, providing a standardized classification tool for documenting VL intubations. It evaluates three components: blade type (Macintosh [M] or Hyperangulated [H]), Percentage of Glottic Opening (POGO), and ease of intubation (Easy [E], Difficult [D], or Failed [F]).^22^ The VCISpain study is a national, multicenter initiative aimed at evaluating the interobserver reproducibility and clinical applicability of the VCI scale in real-world practice across Spain. The study is endorsed by the Spanish Society of Anesthesiology, Resuscitation, and Pain Therapy (SEDAR) and the European Airway Management Society (EAMS). This manuscript presents the study rationale and design to promote transparency, ensure methodological rigor, and encourage constructive feedback prior to implementation.^23^

## Methods

### Objectives

#### Primary Aim

The primary aim of this study is to evaluate the interobserver reproducibility of the VCI scale during tracheal intubation using videolaryngoscopy across multiple centers in Spain.

#### Secondary aims

1.To assess the correlation between the Percentage of Glottic Opening (POGO) and the difficulty of tracheal intubation.2.To evaluate the impact of the operator’s experience level on intubation-related outcomes.3.To determine the incidence of complications associated with tracheal intubation using videolaryngoscopy.

### Study design

The VCISpain study is a prospective, observational, multicenter, and open-label study. This design enables data collection across a diverse range of hospital settings, enhancing the external validity and generalizability of the findings. This protocol was developed in accordance with the STROBE (Strengthening the Reporting of Observational Studies in Epidemiology) guidelines for observational studies.

### Pre-data collection preparations

To ensure consistent and standardized application of the VCI scale across all centers, a comprehensive training and coordination strategy was implemented before the initiation of data collection. All participating anesthesiologists completed a structured, one-hour virtual training session led by the principal investigator ([name]) and study coordinators (PC, MV). The session included a detailed review of the study protocol, proper completion of the Case Report Form (CRF), and specific guidance on applying the VCI scale. Emphasis was placed on protocol adherence, data quality, and ethical considerations.

Each participating hospital received a complete study package containing the CRF, informed consent templates, and all necessary supporting documentation for protocol implementation. To ensure ongoing support, a dedicated online discussion forum was created to allow investigators to submit questions and receive timely clarifications. In addition, monthly virtual meetings are being held with all site investigators to reinforce protocol adherence, resolve methodological concerns, and ensure consistency in the interpretation and documentation of the VCI scale across centers.

All participating centers obtained approval from their ethics committees, ensuring compliance with applicable ethical and regulatory standards throughout the study.

### Eligibility criteria

This study will include adult patients (≥ 18-years-old) with an American Society of Anesthesiologists (ASA) physical status classification of I to III who require TI in a variety of clinical contexts, including diagnostic, therapeutic, or surgical procedures, as well as airway management in the operating room, Post-Anesthesia Care Unit (PACU), Intensive Care Unit (ICU), or emergency department. Eligible patients must undergo TI performed by an anesthesiologist or anesthesia resident participating in the study, and written informed consent must be obtained from the patient or their legal representative prior to the procedure.

### Intervention in the VCISpain study

The intervention begins during the pre-anesthetic consultation or in the anesthetic-surgical preparation area (preoperative holding area), where eligible patients are provided with a detailed information sheet outlining the study objectives, methodology, and potential risks. The investigator anesthesiologists explain the protocol, address any questions or concerns, and ensure patient understanding before obtaining written informed consent.^24^ Participants are informed of their right to withdraw consent at any time. If consent is withdrawn, the participant’s data will be excluded from analysis in accordance with ethical guidelines, thereby respecting their autonomy (Appendices 1–2).

The clinical procedure follows standard practices (Fig. 1). TI is performed using a videolaryngoscope selected based on patient characteristics and the resources available at each center. The responsible anesthesiologist evaluates the TI using the VCI scale, which comprises the following components (Fig. 2):^22^1.Blade Type: The videolaryngoscope is classified as either Macintosh (M) or hyperangulated (H).2.Percentage of Glottic Opening (POGO): The POGO score is recorded at a standardized time point ‒ immediately before advancing the endotracheal tube into the glottis. This measurement reflects the actual glottic view under the force and positioning used during intubation. Investigators are instructed not to record the initial or best view, but rather the view observed at the moment of tube insertion, to ensure consistency and clinical relevance.3.Ease of Intubation: This is categorized as easy (E), difficult (D), or failed (F).a)Easy refers to successful tracheal intubation using the manufacturer’s standard technique for the selected videolaryngoscope, without the need for adjuncts or external assistance.b)Difficult is defined as intubation requiring the use of adjuncts such as a bougie, stylet, or other guiding devices to facilitate tube placement.c)Failed refers to the inability to intubate the trachea using the initially selected videolaryngoscope, necessitating the use of a different videolaryngoscope or an alternative device (e.g., fiberoptic bronchoscope, supraglottic airway, or surgical airway).

**Figure 1 fig0001:**
[figure not shown]
Flowchart.

**Figure 2 fig0002:**
[figure not shown]
VCISpain (Video Classification of Intubation).

Simultaneously, a second anesthesiologist observes the tracheal intubation procedure and independently records the VCI score to assess interobserver reproducibility.

Complications will be prospectively recorded based on predefined clinical criteria, including:^25^ Hypoxemia (SpO_2_ < 90% for ≥ 10 seconds); Esophageal intubation (confirmed by capnography or clinical signs); Dental injury (visible tooth damage); Laryngeal trauma (presence of blood on the blade or tube, hoarseness, or stridor); Bronchospasm or laryngospasm (clinically diagnosed); Failed intubation (requiring a change in device or technique).

If a serious adverse event related to the videolaryngoscope is suspected, the attending physician may temporarily suspend the patient’s participation in the study. Throughout the process, patient safety is prioritized, and each center's standard protocols will be followed in the event of any incident.

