### Outcome measures

#### Primary outcome

The primary outcome is the inter-rater agreement and reproducibility of the VCI scale, defined as the level of concordance between the VCI scores assigned by the anesthesiologist performing the tracheal intubation and an independent observer.

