**General Information**	
Date	
Intubator’s e-mail	
Patient Demographics	
Age	
Sex/Gender	
ASA status	
Weight (kg)	
Height (cm)	

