**Observer Data**	
Role	Resident / Specialist
Years of experience	< 4 / 4–8 / > 8
Prior VL intubations	< 25 / 25–50 / > 50

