### Data collection and management

Data will be collected using a standardized and anonymized physical CRF, independently completed by both the intubating anesthesiologist and the observer during and immediately after the intubation procedure. The collected data will then be managed through the secure electronic platform Research Electronic Data Capture (REDCap), hosted at the University of Navarra (UNAV), ensuring stringent patient confidentiality and data integrity. REDCap offers validated data capture and a transparent audit trail through its comprehensive logging features.

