### Data management workflow

Initial Data Capture: after each procedure, the anesthesiologist will complete the CRF, recording demographic data, procedure variables, and any observed complications.•Data Transfer to REDCap: the pseudo-anonymized data will be entered into the secure REDCap platform. Each patient will be assigned a unique encoding code that is not directly linked to their personal information, ensuring confidentiality.•Ethical and Regulatory Compliance: all data will be collected and stored in full compliance with Good Clinical Practice (GCP) guidelines and current data protection regulations.

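### The printed CRF identifies the intubator but not the observer, so observer ratings cannot be linked to training, traced across cases, or separated by whether the observer helped

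*Protocol article*

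**What the plan says.** All references are to the Protocol article.

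- **Primary outcome (Outcome measures).** Concordance between "the VCI scores assigned by the anesthesiologist performing the tracheal intubation and an independent observer".
- **Second rater (Intervention in the VCISpain study, text after Figure 2).** "a second anesthesiologist observes the tracheal intubation procedure and independently records the VCI score to assess interobserver reproducibility". No training or participation condition is attached here.
- **Training (Pre-data collection preparations).** "All participating anesthesiologists completed a structured, one-hour virtual training session".
- **Eligibility criteria.** "Eligible patients must undergo TI performed by an anesthesiologist or anesthesia resident participating in the study". The observer is not mentioned.
- **Table 1, General Information.** One rater identifier: "Intubator’s e-mail".
- **Table 1, "Observer Data" and Observer VCI.** Role (resident or specialist), years of experience, prior VL intubations, then blade type, POGO band, ease, and adjunct or rescue details. No name, e-mail or code, and no field for help given by the observer.
- **Ease of intubation.** Easy requires success with neither adjuncts nor help from outside.
- **Who completes the form.** Data collection and management says it is "independently completed by both the intubating anesthesiologist and the observer during and immediately after the intubation procedure". Data management workflow says that "after each procedure, the anesthesiologist will complete the CRF", in the singular. Table 1 holds both raters' scores on one form.

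**The concern.** The primary result is a statement about two raters, and the form as printed identifies only one of them. Three things then cannot be done from the CRF data.

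1. An observer's ratings cannot be matched to the training log.
2. Ratings by the same observer cannot be grouped. Nor can one see that a person was intubator in one case and observer in another. An ordinary kappa interval treats the pairs as unrelated; if raters recur and differ in how they score, it is too narrow.
3. Pairs in which the second anesthesiologist helped cannot be told from pairs in which that person only watched. Help bears on the rating itself, because Easy excludes it. An observer who helped knows the category from having taken part and may have influenced it, which sits badly with the independent observer of the primary outcome. Help is more likely when intubation is not easy, so any effect would fall on the less common categories, to which kappa is sensitive.

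This concerns data not collected rather than analysis detail not yet written. A later analysis plan cannot supply a field the form does not carry.

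**Working it through.** **The plan's own figure.** Inputs from Sample size: kappa k = 0.80, difficult intubation p = 0.10, 95% confidence, 5% dropout. For two raters and a binary rating (ease as Easy versus not Easy), the large-sample variance times n is

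V = (1−k)[(1−k)(1−2k) + k(2−k)/(2p(1−p))] = 0.2 × [0.2 × (−0.6) + 0.96/0.18] = 1.0427.

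With n = 1.96² × V/h²:

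- h = 0.055: n = 1,325, and 1,325/0.95 gives 1,395, the stated total.
- h = 0.11: n = 332, and 332/0.95 gives 350.

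So 1,395 matches a half-width of 0.055, not the ± 0.11 stated. That mismatch is a separate matter; here 0.055 serves as the reference precision.

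**Observer's share.** One rating in two: 1,395 of 2,790 planned, or 1,325 of 2,650 after dropout.

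**Cost of untraceable repeat observers (assumed values).** The article gives neither ratings per observer (m) nor an intraclass correlation (ICC). As an approximation, multiply the variance by DE = 1 + (m−1) × ICC, so the half-width is 1.96 × √(1.0427 × DE/1,325).

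| m | ICC | DE | Half-width |
|---|---|---|---|
| 5 | 0.01 | 1.04 | 0.056 |
| 10 | 0.05 | 1.45 | 0.066 |
| 20 | 0.10 | 2.90 | 0.094 |

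Without an observer code, the row that applies cannot be found and the interval cannot be adjusted by observer.

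**Effect of observer involvement (assumed values).** Suppose 10% of cases are Difficult or Failed by the intubator's rating. The plan gives 10% for difficult intubation; applying it to both categories is an assumption. Suppose a watching observer agrees in 82% of these and calls 2% of Easy cases not Easy.

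- Observed agreement: 0.1 × 0.82 + 0.9 × 0.98 = 0.964.
- Observer's not-Easy rate: 0.082 + 0.018 = 0.100.
- Chance agreement: 0.1 × 0.1 + 0.9 × 0.9 = 0.82.
- Kappa: (0.964 − 0.82)/0.18 = 0.800.

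Now let the observer take part in a share s of the Difficult/Failed cases (about 132 of 1,325) and always agree there. Agreement in those cases becomes 0.82 + 0.18s.

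| s | Agreement in Difficult/Failed | Kappa, all pairs |
|---|---|---|
| 25% | 0.865 | 0.828 |
| 50% | 0.910 | 0.856 |
| 75% | 0.955 | 0.882 |

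**Why a restricted kappa is not the remedy.** Dropping the pairs in which the observer took part lowers the Difficult/Failed share to 0.1(1−s)/(1−0.1s), that is 7.7%, 5.3% and 2.7%. With accuracy held at 82% and 2%, kappa among the remaining pairs is 0.779, 0.737 and 0.634. It falls below 0.800 although no rater has become less accurate. Agreement within each category (82% and 98%) does not move with prevalence in this way.

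**The case against.** **Table 1 may not be the whole record.** Exploratory data also points to Appendix 3, which is not shown, and Table 1 prints neither the patient code described under Data management workflow nor a centre field. Site logs might identify observers, and audits, deviation records and a REDCap audit trail are described. This stands: a reader might infer that observers can never be identified, and the documents do not support that. The claim is limited to the CRF as printed. The audit trail answers it only in part, since data are transferred from a physical form and the trail may show who entered a rating rather than who made it. None of these safeguards is said to record assistance.

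**The article already calls for two trained, independent people.** The abstract, the second-rater sentence, the primary outcome and the data collection section all describe two raters or independent completion, and the training sentence is naturally read as covering an observer who fills in the study form. This also stands. A reader might infer that the observer could be the operator, or that only the intubator has to be a participant. Neither follows: the eligibility sentence says which patients' intubations qualify and sets no rule for raters. What remains is that no sentence expressly requires an observer to be trained. A code would not prove independence either.

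**The helper scenario is conjecture.** No passage says that observers assist. Use of an adjunct or a change of device is visible to a bystander, so the 18% miss rate is unsourced, as are the participation shares and perfect agreement by helpers. The move from substantial to almost perfect comes from starting exactly at the 0.80 cut-point. From 0.70 (73% and 3%), shares of 25% and 50% give 0.745 and 0.788, both still substantial. All of this stands, so the figures illustrate and do not estimate. It does not remove the case for recording assistance, which would replace the assumption with data.

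**Conclusion.** The point holds in a limited form. As printed, the CRF has an identifier for the intubator and none for the observer, who supplies half of the primary-outcome ratings, and the article does not expressly require observers to be trained participating raters. From the CRF data alone, observer ratings cannot be linked to training, repeat observers cannot be allowed for in the interval, and assistance cannot be examined.

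The direction and size of any effect on the reported kappa are unknown. The half-widths of 0.056 to 0.094 rest on assumed cluster sizes of 5 to 20 and ICCs of 0.01 to 0.10; the kappas of 0.83 to 0.88 rest on assumed participation and accuracy. Neither range shows that the trial's result will be biased. This is an inexpensive improvement to data capture, not a flaw that invalidates the design.

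**What to change.** 1. Add a pseudonymous rater code for intubator and observer, taken from the training log, in place of the intubator's e-mail.
2. State where the second rater is described that the observer must be on the training log. At the same place, reconcile the description of that person as an anesthesiologist with the CRF option of a resident observer.
3. Add one observer field: took no part / assisted / took over.
4. Use the codes to account for repeated raters in the kappa interval, for example with a bootstrap or variance estimate that respects both raters.
5. Report how often observers assisted, with raw agreement within Easy and within Difficult/Failed by assistance status. Do not rely on a kappa restricted to unassisted pairs.
6. Reconcile the two statements on who completes the form, and say how the two ratings are kept apart on a shared form.

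The cost is a code for each rater and one further field on the CRF and in REDCap, a sentence in the protocol, and a short supplementary table. The sample size does not change. Recruitment was due to start in September 2024, so records already collected may lack the fields unless sites can complete them from their logs; the number left incomplete should be reported.

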#### Secondary outcomes

1.The correlation between the Percentage of Glottic Opening (POGO) score and the difficulty of tracheal intubation.2.The impact of operator experience on VCI scale outcomes, including the influence of training level and prior videolaryngoscopy experience on interobserver agreement and VCI scoring.3.The incidence of tracheal intubation–related complications. While complications such as hypoxemia and laryngeal trauma are included as secondary outcomes, their expected low frequency means that related analyses will remain exploratory and descriptive in nature.

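### Hypoxemia is defined without a starting SpO2 or observation window, so in PACU, ICU and emergency patients pre-existing hypoxemia can be counted as an intubation complication and cannot be identified afterwards

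*Protocol article*

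**What the plan says.** - **Definition.** In Methods, *Intervention in the VCISpain study* (text after Figure 2), the article states "Complications will be prospectively recorded based on predefined clinical criteria" and lists "Hypoxemia (SpO_2_ < 90% for ≥ 10 seconds" first.
- **Who can enter.** *Eligibility criteria* covers "airway management in the operating room, Post-Anesthesia Care Unit (PACU), Intensive Care Unit (ICU), or emergency department". It limits entry to an "American Society of Anesthesiologists (ASA) physical status classification of I to III" and adds that "written informed consent must be obtained from the patient or their legal representative prior to the procedure". It states no exclusion for low SpO2 or respiratory failure.
- **What the item feeds.** *Secondary aims*, item 3: "To determine the incidence of complications associated with tracheal intubation using videolaryngoscopy". *Secondary outcomes*, item 3: "The incidence of tracheal intubation–related complications", with the qualification that "their expected low frequency means that related analyses will remain exploratory and descriptive in nature".
- **What is recorded.** The Complications block of the CRF (Table 1) has one desaturation line, marked below 92%, with no duration. Neither Table 1 nor the data domains under *Exploratory data* includes an SpO2 value before laryngoscopy. Place of intubation is recorded.

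**The concern.** An incidence of procedural complications should count events that begin with, or are worsened by, the procedure. An absolute threshold achieves this only if patients start above it. In theatre most probably do. In the ICU or emergency department, some patients need a tube because oxygenation has already failed. A patient at 86% before the blade enters the mouth satisfies the written criterion with no contribution from the laryngoscopy.

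Without a rule for this case, each investigator chooses between the literal criterion and personal judgement about whether the low value is intubation-related. Across the 35 hospitals named in the Discussion, the reported rate could then vary with case mix and local habit as well as with what happens during intubation. Because the analysis is descriptive, the rate itself is the result, so misclassification goes straight into it.

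**Working it through.** The plan gives no figure for this outcome, so there is none to reproduce. The check has two parts.

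**1. Can the recorded data separate pre-existing from new hypoxemia?**

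| Needed to call the event new | Definition in the text | Printed CRF |
|---|---|---|
| SpO2 before laryngoscopy | not stated | no field |
| Required fall from the start | not stated | no field |
| Start and end of observation | not stated | no field |
| Threshold | below 90% | below 92% |
| Duration | at least 10 seconds | none |

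They cannot. The last two rows also conflict. A patient whose lowest value is 91%, or who dips below 90% for a few seconds, meets the CRF line but not the definition, so the defined event cannot be derived from the field. The higher CRF cut-off would also take in more patients who were low at the start.

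**2. How large could the effect be?** This is a sensitivity calculation. Only the sample size comes from the documents.

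- Evaluable patients: *Sample size* gives 1,395 including 5% dropout; 1,395 × 0.95 = 1,325.
- *s*, share of ICU and emergency cases: assumed 2% to 20%.
- *b*, share of those below 90% before laryngoscopy: assumed 5% to 30%.
- *r*, true new-onset rate: assumed 3.0%.
- Every such patient is assumed to be recorded as a complication.

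Pre-existing cases counted = 1,325 × *s* × *b*. 
Reported rate = *s·b* + (1 − *s·b*) × *r*.

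| *s* | *b* | Cases counted | Reported rate |
|---|---|---|---|
| 2% | 5% | 1,325 × 0.001 = 1.3 | 0.001 + 0.999 × 0.03 = 3.1% |
| 5% | 10% | 1,325 × 0.005 = 6.6 | 0.005 + 0.995 × 0.03 = 3.5% |
| 10% | 20% | 1,325 × 0.02 = 26.5 | 0.02 + 0.98 × 0.03 = 4.9% |
| 20% | 30% | 1,325 × 0.06 = 79.5 | 0.06 + 0.94 × 0.03 = 8.8% |

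Pre-existing cases outnumber new ones only when *s·b* exceeds *r*/(1 + *r*) = 0.03/1.03 = 2.9%. That needs, for example, a 10% ICU and emergency share with 30% of them already hypoxemic.

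**The case against.** **Outcome wording.** The aim and the outcome are limited to complications associated with, or related to, intubation. On that wording, an investigator could properly decline to record a low value that was present beforehand. This stands against a stronger reading that a reader might infer, namely that such patients *are* counted or that sites *must* record them. The article says neither. What remains is that it gives no rule for deciding that a low SpO2 is intubation-related, and no data from which the decision could be checked.

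**Condensed article.** The complication criteria carry a literature citation, the data domains refer to an appendix, and sites were trained in completing the CRF. Timing rules may sit in material not shown. This lowers confidence, but the article prints both the operational rule and the CRF, and the gap is in what is printed.

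**Exposed group.** ASA I to III and prior written consent plausibly keep out many patients in acute respiratory failure. *Intervention in the VCISpain study* also places the consent discussion in the pre-anesthetic consultation or preoperative holding area. This stands, and it is why the effect is probably small. Consent by a legal representative and the ICU and emergency settings mean that the group is not empty.

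**Descriptive status.** The analysis is secondary and exploratory, which limits the consequences. It does not remove the bias in the rate.

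**Bronchospasm and stridor.** A reader might extend the point to these. The extension is weak: stridor appears only as a sign of laryngeal trauma, and bronchospasm is left to clinical diagnosis, which allows judgement on onset.

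**Conclusion.** The point holds in a limited form. As printed, the definition permits pre-existing hypoxemia to be counted, and the CRF offers no way to find those cases later. The descriptive incidence under aim 3 can therefore be biased upward. The inter-rater agreement that forms the primary outcome is not affected.

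The documents give no ICU or emergency share, no starting SpO2 distribution and no expected hypoxemia rate, so the bias cannot be sized from them. The range of about 1 to 80 patients rests wholly on the assumptions shown and on every such patient being recorded. The entry limits argue for its lower part. A reader might infer from the top of the range that false events could match or exceed true ones. That needs a large non-theatre share and a high proportion already hypoxemic, and the documents support neither.

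The conflict between below 90% for at least 10 seconds in the text and below 92% with no duration on the CRF needs no assumptions. It has to be settled first, because at present the study has no single hypoxemia threshold.

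**What to change.** 1. Reconcile the definition in *Intervention in the VCISpain study* with the desaturation line in Table 1, for both level and duration. Which threshold applies is for the sponsor to decide.
2. Add two CRF fields: the last SpO2 before laryngoscope insertion and the lowest SpO2 during the attempt. State the observation window.
3. Report new-onset hypoxemia among patients at or above the reconciled threshold at the start. Report patients already below it as a separate group, including any further fall. Simply excluding them would lose real deterioration in those at highest risk.
4. Give incidence by place of intubation, which is already collected. The printed form has no separate PACU option, so those cases would fall under its *Other* category.
5. For patients enrolled before the fields exist, report by place only and state the limitation.

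**Cost.** One or two extra fields, missing for earlier patients (recruitment was planned to start in September 2024), a CRF change to carry across all sites, and a slightly smaller denominator for new-onset events. The monthly site meetings and REDCap are already in place to carry the change.
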